### Data collection at follow-up

Follow-up data will be collected 2 and 6 weeks, 4, 8, 12 and 24 months after the intervention (Table 1). At each time point the OSS [14, 15], the QuickDASH upper extremity score [16, 17], the EQ-5D-5L general health score [18, 19] and VAS for pain at rest, during activity, and at night will be filled in. To perform the 2 and 6 week and 8 and 12 month follow-ups patients will receive an e-mail with a link to a website, where they can fill in the study questionnaires at their computer at home.

At clinical follow-ups after 4 and 24 months study scores will be filled in on a computer/tablet at the hospital. The blinded assessor will register all treatment related adverse events by asking and by consulting each patient’s adverse event diary. The adverse event diary will be handed out to the patients on treatment day and will have to be kept over the entire 24-month follow-up period. Patients will be asked to enter in the diary any changes of their health condition that theiy perceive as an adverse event. The type of the event, its date of occurrence, its duration and its severity (on a 5 point Likert scale ranging from mild to severe) will have to be given. In case of a serious event, the hospital will have to be contacted immediately. If an adverse event requires treatment this will be recorded by the physician who is responsible for patient follow-up. The use and the dosage of prescription analgesics during the post treatment period will be recorded. An X-ray of the shoulder will be performed and, if still visible, the calcific deposit will be measured and classified according to Molé [13], blinded for baseline results.

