### Sample size

Calculation of sample size was performed for an ANOVA of our primary outcome, which is the result on the OSS at 4 month follow-up. To detect a minimally important difference of 4 (SD 7) points [26] with a power of 90%, a 2-sided significance level of 0.05, 60 patients are required in each treatment group. To compensate for expected 15% drop-outs, we plan to include 70 patients in each treatment group. A supplementary analysis showed that this sample size also will be sufficient for pairwise post hoc *t*-test analyses (1 versus 2, 2 versus 3 and 1 versus 3), still with a significance level after Bonferroni correction of 0.017 but with a power of approximately 80%.

The actual statistical analysis of the interventions on primary outcome will be conducted using linear mixed models for repeated measurements adjusted for outcome measure at baseline. It is expected to give a slightly higher statistical power than an ANOVA.

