### Statistical analysis

Demographic baseline data will be expressed for categorical variables as number of cases and for continuous variables by means with SD (if normally distributed) or by medians with range (if not normally distributed).

A linear mixed model for repeated measurements will be used for analysis. Because of an expected large number of crossovers after 4 months, the primary analysis will be performed on results up to 4 month follow-up and a secondary analysis on results up to 24 month follow-up. Analyses will be performed adjusted for baseline differences of the OSS and according to intention-to-treat. The linear mixed model will be estimated using linear maximum likelihood and include a random intercept, measure of the OSS at baseline as a covariate and observation time after intervention and type of intervention as factors. Mean differences (95% CI) between groups at 4 months follow-up will be presented from the linear mixed model to assess difference between interventions. A 2-sided *p*-value ≤ 0.05 is considered significant. Post-hoc pairwise comparisons for the primary outcome will be performed with p-value adjustments according to Bonferroni. Missing values will be handled by using mixed model analysis. Supplementary per-protocol analyses will be performed. A similar statistical analysis as described for the OSS will be used for the continuous secondary outcomes (QuickDASH, EQ-5D-5L).

Categorical variables will be expressed as numbers and percentages, and differences between groups will be analysed by the Chi^2^ or Fisher’s exact test. Possible associations between categorical baseline variables and outcomes will be explored by logistic regression analysis.

All subgroup analyses will be exploratory in nature and are planned for the size of the calcification at baseline (≤12.5 mm versus >12.5 mm), the volume of the removed material (≤0.1 ml versus > 0.1 ml), and the results on the Stanford expectation of treatment scale (positive expectancies versus negative expectancies). Selection of the threshold values for the size of the calcification at baseline and for the volume of the removed material are based on the findings of an unpublished pilot study from our institution.

Clinical safety will be investigated by assessing adverse events in a descriptive manner.

The statistician responsible for data analyses will blinded from the treatment allocation until completion of analyses.

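### The only covariance term stated for the primary mixed model is a random intercept, which ties the 4-month standard error to the spread at 2 and 6 weeks

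*Protocol article*

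**What the plan says.** The Statistical analysis section describes a linear mixed model for repeated OSS measurements, "estimated using linear maximum likelihood and include a random intercept". Baseline OSS is a covariate, with "observation time after intervention and type of intervention as factors". The headline result comes from this model: "Mean differences (95% CI) between groups at 4 months follow-up will be presented from the linear mixed model".

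The same section limits the primary model in time: "the primary analysis will be performed on results up to 4 month follow-up". Data collection at follow-up gives the schedule: "Follow-up data will be collected 2 and 6 weeks, 4, 8, 12 and 24 months after the intervention". The primary model therefore holds three post-baseline visits, at 2 weeks, 6 weeks and 4 months. The model is also the stated approach to incomplete data: "Missing values will be handled by using mixed model analysis".

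No random slope, residual covariance structure, visit-specific variance or robust standard error is mentioned. The Sample size section gives a single SD, in "minimally important difference of 4 (SD 7) points", and none by visit.

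**The concern.** A random intercept with independent, equal-variance residuals implies compound symmetry: one variance for every visit and one covariance for every pair of visits. The model then estimates a single total variance from all three visits and applies it to the 4-month contrast. That is harmless if the spread is constant. If it is not, the interval reported for 4 months has a width that belongs partly to other visits.

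The article itself gives reason not to take constant spread for granted. The Background describes a course that is often self-limiting over several months in some patients and persistent in others. The Scoring instruments section bounds the OSS at 48. Spread could grow as patients diverge, or shrink as many approach the ceiling. At stake is the calibration of the primary confidence interval and of the Bonferroni-adjusted pairwise tests.

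**Working it through.** **1. The plan's own figure.** The Sample size section states a difference of 4, SD 7, "with a power of 90%, a 2-sided significance level of 0.05, 60 patients are required in each treatment group". For a three-group ANOVA with means 0, 0, 4, the noncentrality at n = 60 is 60 × [2 × (4/3)² + (8/3)²] / 49 = 13.06. This gives 90.4% power, and 60 is the smallest n that reaches 90%. The figure reproduces, and the point below does not touch it.

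**2. Inputs.** n = 60 per group and a 4-month SD of 7 come from the Sample size section. The SDs at 2 and 6 weeks are my assumptions. The error rates depend only on the ratio of the pooled SD to the 4-month SD.

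**3. Formulas** (complete data, time-by-intervention term included).
- Standard error (SE) from 4-month variance only: 7 × √(2/60) = 1.278.
- SE under the random intercept: pooled SD × √(2/60), where pooled SD = √(mean of the three visit variances).
- r = pooled SD / 4-month SD.
- Actual level of a test at nominal α: 2 × [1 − Φ(z × r)], with z = 1.960 for α = 0.05 and z = 2.394 for α = 0.05/3 = 0.0167.

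Example for 5/6/7: pooled SD = √[(25 + 36 + 49)/3] = √36.67 = 6.055; SE = 6.055 × 0.1826 = 1.106; r = 6.055/7 = 0.865; 1.960 × 0.865 = 1.695, so the actual level is 9.0%.

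| Assumed SD at 2 wk / 6 wk / 4 mo | Pooled SD | Model SE | r | Actual level, nominal 5% | Simulated, nominal 5% | Actual level, nominal 1.67% |
|---|---|---|---|---|---|---|
| 7 / 7 / 7 | 7.000 | 1.278 | 1.000 | 5.0% | 5.2-5.3% | 1.7% |
| 6 / 6.5 / 7 | 6.513 | 1.189 | 0.930 | 6.8% | 6.9-7.2% | 2.6% |
| 5 / 6 / 7 | 6.055 | 1.106 | 0.865 | 9.0% | 9.6-9.7% | 3.8% |
| 9 / 8 / 7 | 8.042 | 1.468 | 1.149 | 2.4% | 2.5-2.7% | 0.6% |

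The simulated column is from 20,000 replicates per setting, three arms of 60, complete data and no baseline covariate. Its two values are for equal correlations (0.6 throughout) and for unequal ones (0.7 between 2 and 6 weeks, 0.6 between 6 weeks and 4 months, 0.4 between 2 weeks and 4 months). In the same runs, a test using the 4-month variance alone rejected in 4.7% to 5.6% of replicates.

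**4. Check with a fitted model.** One data set of 180 patients was simulated with SDs 5/6/7 and fitted by maximum likelihood with a random intercept and time-by-arm terms. The 4-month contrast had SE 1.167. The pooled-variance formula on the same data gives 1.167; the 4-month data alone give 1.299. The model does use the pooled variance.

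**5. What does not drive the result.** With SDs 7/7/7 and the unequal correlations, the level was 5.2%, much the same as with equal correlations. Maximum likelihood against REML moves the SE by about 1%: 1.278 × √(177/180) = 1.267, against a simulated mean of 1.266.

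**The case against.** The strongest reply is that the article says the model includes a random intercept; it does not say that nothing else is included. Residual structure is a detail that a full protocol or analysis plan may set, and neither is shown. This stands as a limit: the point is about the model as stated with customary residuals. It does not remove the point, because the article does specify the covariance as far as it goes, and what it specifies is the restrictive choice.

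The second reply is that size and direction rest on assumed SDs. That also stands. The only SD in the article is 7. Nothing there says that early visits vary less than 4 months, and the reverse case makes the test conservative.

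Third, the calculation presumes a time-by-intervention term, which the article does not list. Without one, the reported 4-month difference is an average over the three visits, with a smaller SE still (0.980 in the data set of step 4). That is a separate and larger matter. The present point remains after it is repaired.

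A reader might also infer three stronger things that are not supported. Maximum likelihood does not cause the constraint; its own effect is about 1% of the SE. Unequal correlation between visits does not materially disturb the primary test when data are complete. With missing 4-month values the correlations do enter, but I put no size on that. The visits after 4 months do not affect the primary interval, because the primary model stops at 4 months.

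**Conclusion.** The point holds in a limited form. As stated, and with independent equal-variance residuals, the primary model assumes equal variance at 2 weeks, 6 weeks and 4 months and pools the 4-month SE accordingly. If the assumption fails, the primary interval and p-value are miscalibrated: about 7% for SDs 6/6.5/7, 9-10% for 5/6/7 and 2.5% for 9/8/7, against a nominal 5%. There is no error if the SDs are equal.

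These figures assume complete data, a time-by-intervention term and the invented early-visit SDs. It would be tempting to conclude that the trial's primary test is anti-conservative. The article does not support that, since the direction is unknown. What can be said is that the level of the primary test depends on an equality of variances that the article does not justify and that the analysis does not need.

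**What to change.** For the primary model, replace the random intercept by an unstructured covariance over the three post-baseline visits, fitted by REML. State in advance a simpler structure to use if the fit does not converge, and choose one that still allows unequal visit variances, such as a heterogeneous Toeplitz structure. The 4-month contrast should be read from a model that contains the time-by-intervention term.

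The unstructured form has six covariance parameters (three variances, three covariances) where the random intercept has two. Four extra parameters are a small price with about 180 to 210 patients. Otherwise the change is one of wording, with no effect on sample size, visits or data collection.

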### Outcome assessment

The study’s primary outcome measure is the OSS with the outcome at 4 months as the result of primary interest. Secondary outcomes are the results on the OSS at the other points of follow-up, results of the other study scores at all points of follow-up and the number of patients in each treatment group who change treatment during the study.

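### As listed, the primary mixed model has no time-by-treatment term, so it gives one group difference common to all visits and not the promised 4-month difference

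*Protocol article*

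**What the plan says.** All references are to the protocol article.

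- **Target.** Outcome assessment: "The study’s primary outcome measure is the OSS with the outcome at 4 months as the result of primary interest". OSS at the other visits is a secondary outcome, as are the other scores at all visits.
- **Visits.** Data collection at follow-up: "Follow-up data will be collected 2 and 6 weeks, 4, 8, 12 and 24 months after the intervention".
- **Data used.** Statistical analysis: "the primary analysis will be performed on results up to 4 month follow-up". The model rows are therefore the 2-week, 6-week and 4-month visits. A secondary analysis runs to 24 months.
- **Model.** Statistical analysis: "The linear mixed model will be estimated using linear maximum likelihood and include a random intercept", followed by the fixed part, "measure of the OSS at baseline as a covariate and observation time after intervention and type of intervention as factors".
- **Result to be reported.** Same section, next sentence: "Mean differences (95% CI) between groups at 4 months follow-up will be presented from the linear mixed model".
- **Sample size.** Computed for an ANOVA of the 4-month OSS alone: "To detect a minimally important difference of 4 (SD 7) points" "with a power of 90%, a 2-sided significance level of 0.05, 60 patients are required in each treatment group". Bonferroni pairwise comparisons at 0.017 are stated to have roughly 80% power.

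Neither the Sample size section nor the Statistical analysis section names a time-by-treatment interaction.

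**The concern.** With time and intervention entered only as main effects, the fitted arm profiles are parallel. The model then holds one treatment difference per pair of arms, and the value it gives at 4 months is the same as at 2 and 6 weeks. The listed terms and the promised 4-month difference do not fit together.

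At stake is what the primary result measures. If the arms separate early and converge by 4 months, early benefit is carried into the reported 4-month figure. If they separate late, the 4-month effect is diluted. The same gap affects the 24-month model, where one difference would be shared by six visits although the Aims section states a separate 2-year comparison. It also affects QuickDASH and EQ-5D-5L, which are to be analysed in a similar way.

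**Working it through.** **Inputs from the protocol.** Difference 4, SD 7, 60 analysed per arm, pairwise level 0.017 (0.05/3 = 0.0167), visits at 2 weeks, 6 weeks and 4 months.

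**Assumed, because the protocol gives none.** Within-patient correlation ρ of 0.5 (range 0.3 to 0.7), SD 7 at each visit, and the courses of the group difference used below. Baseline adjustment is ignored in the closed forms.

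**1. The plan's own figure.** One-way ANOVA with three groups, means (0, 0, 4), SD 7, alpha 0.05. The sum of squared deviations from the grand mean is 10.67, so the noncentrality is 60 × 10.67/49 = 13.06. Power is 90.4%, and 60 is the smallest n per group that reaches 90%. The stated 60 is reproduced, and it rests on the 4-month value alone.

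**2. Direct pairwise comparison at 4 months.** SE = 7 × √(2/60) = 1.278. For 4 points at 0.017, power is Φ(4/1.278 − 2.387) = 77% (76% with the t distribution).

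**3. What the listed model estimates.** In one complete simulated data set (time and treatment only, random intercept, maximum likelihood), the differences at the three visits were −2.840, 0.006 and 4.306. Their mean is 0.4907. The model's treatment coefficient was 0.4907.

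**4. Precision of that average.** SE = √[(2 × 49/60) × (1 + 2ρ)/3].

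- ρ = 0.3: √(1.633 × 0.533) = 0.93
- ρ = 0.5: √(1.633 × 0.667) = 1.04
- ρ = 0.7: √(1.633 × 0.800) = 1.14

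**5. Consequences for assumed courses, complete data.** The first row uses level 0.0167, the others 0.017.

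| True difference at 2 wk, 6 wk, 4 mo | Reported for 4 months | Chance of significance, ρ = 0.3 / 0.5 / 0.7 |
|---|---|---|
| 6, 4, 0 | (6+4+0)/3 = 3.33 | 88% / 79% / 70% |
| 0, 0, 4 | 4/3 = 1.33 | 17% / 13% / 11% |
| 0, 4, 4 | 8/3 = 2.67 | 68% / 57% / 48% |
| 4, 4, 4 | 4 | 97% / 93% / 87% |

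For example, in the first row at ρ = 0.5: Φ(3.33/1.04 − 2.394) = Φ(0.80) = 79%.

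**6. Missing 4-month values.** Suppose 15% are missing at random and ρ = 0.5. Up to a common factor, each visit of a complete patient has weight 1/(1 + 2ρ) = 0.5, and each visit of a patient with only two visits has weight 1/(1 + ρ) = 0.667. Each early visit then gets 0.85 × 0.5 + 0.15 × 0.667 = 0.525, and the 4-month visit gets 0.85 × 0.5 = 0.425. The total is 1.475, so the 4-month visit carries 0.425/1.475 = 29% instead of 33%. The course 0, 0, 4 would be reported as about 1.15, and 6, 4, 0 as about 3.56.

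**7. With the interaction added.** Over 40 simulated complete data sets per course (ρ = 0.5), the 4-month contrast averaged 4.3 for 0, 0, 4 and −0.2 for 6, 4, 0. The listed model gave 1.6 and 3.2. Apart from simulation error, the interaction model recovers the true 4-month values of 4 and 0.

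**The case against.** The strongest reply is that the protocol does not exclude an interaction. It says what the model will include, not that nothing else enters, and the very next sentence promises differences at 4 months, which only make sense with a time-by-treatment term. The Sample size section also expects only slightly more power than an ANOVA. Pooling visits under a constant 4-point effect would raise pairwise power from 76-77% to 87-97%, which is more than slight. A journal article condenses, and the analysis plan is not shown.

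Much of this stands. A reader might infer that the trial will analyse the wrong quantity, or that its primary estimate is biased and its error rate broken. The document does not support either inference:

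- An interaction may well have been intended and left out of the list.
- If the group difference is constant over the three visits, the pooled estimate is unbiased and more precise. If the arms are equal at every visit, the error rate holds.
- The courses in the table are illustrations. The protocol gives none.
- The barbotage and steroid arms receive the same triamcinolone injection, so an early steroid benefit should largely cancel between them. It bears mainly on the comparisons with placebo.

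What does not stand is that this is only detail left to another document. The article fixes the terms of its primary model, and those terms as written cannot produce the estimate it announces. Nor does it assume a constant difference: the Discussion describes the two active arms as resting on different therapeutic principles.

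**Conclusion.** The concern holds for the model as listed. It yields one difference common to 2 weeks, 6 weeks and 4 months, which is exactly the simple mean only with complete data, and not the 4-month difference that is declared primary and that the sample size is built on.

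The harm is conditional. It is nil under a constant difference and can be large otherwise: under the assumptions above, about 3.3 points reported where the 4-month truth is 0, or about 13% power (11-17% over the correlation range) for an effect that a direct comparison would detect with 76-77%. These sizes depend chiefly on the assumed courses, less on the correlation. Either the list of terms is incomplete or the promised estimate is mislabelled. Leaving both readings open would allow the choice to be made after the results are known.

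**What to change.** Before unblinding, add to the protocol or analysis plan:

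- The primary model includes a time-by-treatment interaction, with time as a categorical factor.
- The primary estimates and tests are the between-arm contrasts at 4 months from that model. An overall test, if kept, is of equal arms at 4 months.
- The 24-month model and the secondary-score models are specified in the same way, with contrasts at the visits of interest.

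Baseline-by-time terms are optional.

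The cost is a sentence or two and some apparent precision: at correlation 0.5 and before baseline adjustment, the SE is about 1.28 for a direct 4-month contrast against 1.04 for the pooled one. The pooled figure is valid for 4 months only if the difference is constant. No sample size change follows, since 60 per arm was computed for the 4-month value alone.

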### Intervention

An orthopaedic surgeon (2 hospitals), a radiologist (1 hospital), or a specialist in physical medicine (3 hospitals), all with at least 5 years of experience in diagnostic and interventional ultrasound of the shoulder will conduct the allocated interventions. To ensure consistency a video of the procedure was produced and send to all trial sites (Additional file 1: Video barbotage procedure).

Interventions will be performed with the patient in supine position. The arm will be internally rotated to a degree that the treating physician considers to be the most favourable for the puncturing of the calcific deposit (usually arm on the back). An opaque sheet will be used to block the patient’s view of the screen of the ultrasound machine. After sterile skin preparation, with a 7 to 14 MHz transducer wrapped in a sterile drape, and by using sterile jelly, the calcific deposit will be sonographically identified, usually on the lateral transversal view. A 21-gauge needle will be introduced into the shoulder under sonographic guidance, and the pathway and the subacromial-subdeltoid bursa will be anesthetized with an injection of 10 ml of 1% lidocaine hydrochloride with adrenaline 5 μg/ml.

In patients randomized to barbotage a new 18-gauge needle connected to a 5 ml syringe with 4 ml of saline solution will be used to puncture the calcification using freehand technique under continuous sonographic monitoring. With the tip of the needle placed in the centre of the deposit, the calcification will be flushed. If backflow of calcific material can be identified in the syringe, lavage of the deposit will be performed by successive propulsion and aspiration with the syringe plunger. Extracted calcium can be visualized in the syringe as a cloudlike substance that settles at the bottom of the barrel. To avoid reinjection of the calcium into the deposit, the needle and the syringe will be hold in the horizontal plane during the procedure. The syringe will be substituted when the fluid has become cloudy and the procedure will be repeated until the backflow becomes clear. At the end of the procedure the content of the syringes will be poured into a measuring cup and, when settled at the bottom of the cup, the volume of the extracted calcium will be estimated. In cases where no material can be extracted, repeated perforation of the deposit will be performed to possibly initiate or accelerate spontaneous resorption.

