In patients randomized to the steroid group or to the placebo group, the tip of the 18-gauge needle will be placed in the soft parts outside of the rotator cuff and movements mimicking the lavage procedure will be performed. A lavage procedure usually takes 5 min and a similar time period will be used for the mimicking manoeuvre.

Finally in all three groups, under sonographic monitoring, a new 21-gauge needle will be introduced into the subacromial bursa and 9 ml of Lidocaine hydrochloride 10 mg/ml and 1 ml of Triamcinolone 20 mg/ml (in the barbotage and the steroid group) or 10 ml of Lidocaine hydrochloride 10 mg/ml (in the placebo group) will be injected into the subacromial bursa.

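### Removed calcium volume is a post-randomisation result that exists only in the barbotage arm, so it cannot define a treatment-effect subgroup

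*Protocol article*

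**What the plan says.** The Statistical analysis section introduces the subgroup work with "All subgroup analyses will be exploratory in nature and are planned for the size of the calcification at baseline". It then adds "the volume of the removed material (≤0.1 ml versus > 0.1 ml") and finally the result on the expectation scale (SETS). The cut-offs for deposit size and removed volume come from an unpublished pilot study. The text does not say that the volume analysis is limited to one arm or that it is non-randomised.

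The Intervention section says where the volume comes from. The lavage description begins "In patients randomized to barbotage a new 18-gauge needle connected to a 5 ml syringe with 4 ml of saline solution will be used", and at the end of that procedure "the volume of the extracted calcium will be estimated". If nothing comes out, a different manoeuvre follows: "In cases where no material can be extracted, repeated perforation of the deposit will be performed". In the steroid and placebo groups, by contrast, "the tip of the 18-gauge needle will be placed in the soft parts outside of the rotator cuff", and the lavage is only imitated.

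On blinding, the Statistical analysis section ends: "The statistician responsible for data analyses will blinded from the treatment allocation until completion of analyses". The Blinding section also says that the analysing statistician is blinded to treatment.

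**The concern.** A subgroup analysis of a treatment effect needs a variable that is defined in every arm and cannot be altered by allocation. Only then are the arms within each class still a randomised comparison. Deposit size at baseline and SETS, which is completed before treatment, meet this condition. Removed volume does not, yet it stands between them in the same list with the same status.

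The risk lies in interpretation. The Discussion describes removal of the deposit as what barbotage adds to the anti-inflammatory injection, and gives better knowledge of mechanisms as an aim. If the randomised comparison shows no difference, a natural next statement is that barbotage helps when material is actually removed. A volume subgroup would appear to support that statement without being able to do so.

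**Working it through.** **1. Counts.** From the Sample size section and the 1:1:1 allocation: 3 × 70 = 210 patients, of whom 2 × 70 = 140 are in the sham arms. At most 210 − 140 = 70 can have a measured volume.

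**2. Order of events.** Patients are randomised on the day of the intervention and the group is then displayed (Randomisation). The procedure follows, and the volume is estimated at its end (Intervention). The variable is therefore post-randomisation.

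**3. Who can fall in each class.**

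| Class | Barbotage | Steroid (sham) | Placebo (sham) |
|---|---|---|---|
| >0.1 ml | those with higher yield | none possible | none possible |
| ≤0.1 ml | lower yield, including no extraction | no value, or all if coded 0 | no value, or all if coded 0 |

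The article does not say how sham patients would be coded. It does not matter. With no value, both classes hold barbotage patients only. With a coded zero, the ≤0.1 ml class sets a selected part of one arm against the whole of the other two. Neither gives a randomised contrast. This result needs no assumption.

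**4. Split within the barbotage arm.** High yield against low yield can be computed, but yield was not randomised. The low class also includes patients who had repeated perforation because nothing could be extracted, so the classes differ in procedure as well as in whatever determined the yield.

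**5. Blinding.** Only one arm can have volumes above zero. A data file that contains the variable identifies that arm, even if the arms are coded A, B and C.

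**6. Possible size of the selection effect (illustration; the documents give no figure).** Assumptions: no true difference between barbotage and steroid; SD 7, and 60 analysed per arm (both figures from the Sample size section); half of the barbotage arm in the high class; normal variables; correlation r between removed volume and outcome, with r assumed. For a normal variable split at its mean, the expected excess of the high class over an unselected arm is

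SD × r × √(2/π) = 7 × 0.798 × r = 5.59 × r.

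This gives 0, 1.12, 1.68 and 2.79 OSS points at r = 0, 0.2, 0.3 and 0.5. A simulation with 4,000 repetitions per value of r gave:

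| r | High class minus steroid arm | False-positive rate at nominal 0.05 | High minus low class within barbotage | Share of within-arm tests with p < 0.05 |
|---|---|---|---|---|
| 0 | 0.0 | 5% | 0.0 | 5% |
| 0.2 | 1.1 | 10% | 1.11 + 1.11 = 2.2 | 22% |
| 0.3 | 1.6 | 18% | 1.62 + 1.70 = 3.3 | 45% |
| 0.5 | 2.8 | 42% | 2.75 + 2.81 = 5.6 | 90% |

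The planned minimally important difference is 4 points. The illustration shows only that an appreciable difference can arise in either contrast without any treatment effect. It does not estimate what will happen in this trial.

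**7. The plan's own sample size** is not in dispute. A three-group ANOVA with means 0, 0 and 4, SD 7 and alpha 0.05 needs 60 per group (power 0.904), which matches the article.

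**The case against.** The strongest reply is that the article nowhere promises a comparison of high-volume patients with sham patients. It says only that exploratory analyses are planned for three variables. Since the Intervention section describes volume only for barbotage patients, the sensible reading is a split of that arm by yield, which suits an interest in mechanisms. That much stands: a reader might infer a planned contrast of the >0.1 ml class with sham, but the text does not state one. It also does not exclude one, and the placement between two true baseline subgroups invites it. Even on the narrower reading, the analysis is an association within one arm and not a subgroup analysis of treatment effect.

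A second reply is that the analyses are labelled exploratory and the cut-off was fixed in advance. Both facts lower the weight that a result can carry. Neither supplies a comparator or removes the selection.

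A third reply concerns prognosis. A reader might infer that deposits yielding more material are softer and would have improved anyway. The documents do not say so. The Background describes spontaneous resorption with relief of symptoms, which makes some link plausible, but nothing ties extracted volume to outcome. Entry is limited to Molé types A to C, and recent spontaneous release is an exclusion. At r = 0 the bias in the illustration is nil.

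Finally, a reader might infer a flat contradiction with the blinding pledge. That goes too far. The variable can be held back, and release order is often set elsewhere. But the sentence covers analyses without exception, so as worded it also covers the volume analysis, which cannot be done without revealing the barbotage arm.

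**Conclusion.** The point holds as a structural fault in one exploratory item. Removed volume is measured after randomisation, in at most 70 of 210 patients, all in one arm, so it cannot define a subgroup for a treatment effect. This follows from the document alone. A fuller analysis plan could redefine or withdraw the item, but could not give the >0.1 ml class a randomised comparator.

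Three limits apply. A comparison with sham is not expressly planned. The size of any selection bias is unknown: the range of 0 to 2.8 points rests on assumed correlations of 0 to 0.5 and on an even split of the arm. The conflict with blinding arises only if the variable is released or analysed while the statistician is still meant to be blinded. The primary analysis of the OSS at 4 months is unaffected. The change is worth making because it is cheap and closes the way to a claim, based on selected responders, that the randomisation cannot support.

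**What to change.** In the Statistical analysis section:

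- Remove removed volume from the list of subgroup analyses, leaving baseline deposit size and SETS.
- State separately that removed volume will be described only within the barbotage group, as an exploratory, non-causal association with outcome, adjusted for baseline OSS and baseline deposit size, and with no comparison to either sham group.
- State that the variable is withheld from the statistician until the blinded between-arm analyses are complete. Amend the blinding sentence so that it covers those analyses and not the later description within the barbotage arm.

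The cost is a change of wording, an agreed order of data release, and one exploratory comparison given up. No valid randomised comparison is lost, and sample size and data collection stay as they are.
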